### Secondary outcome

Amputation rates and the reduction of lesions that do not heal will be assessed, with an evaluation of statistical significance between the groups. The evaluation of the domains of the SF-36 quality of life questionnaire will also be done in both groups. The data from this questionnaire upon admission and after 3 months of follow-up will be compared.

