**Methods:**

A non-blind randomized clinical study will be conducted in the city of Imperatriz, Maranhão state, Brazil, from 2019 to 2020, in diabetic patients with chronic foot ulcers (classified as Wagner grades 2, 3 and 4, persisting for more than 1 month). The outpatient follow-up for diabetic foot patients will be done at the Unified Health System, with a sample size of 120 patients (the randomization allocation will be 1:1, being 60 patients for each arm). Half of the patients will receive standard treatment, i.e. dressings, debridement, antibiotics and load relief, along with HBOT (HBOT group), and the other half will receive only standard treatment (control group). The patients of the HBOT group will be evaluated upon admission, after 10, 20, 30 and 35 HBOT sessions, and after 6 months and 1 year. The patients of the control group will also be evaluated at equivalent periods (upon admission, after 2, 4, 6 and 7 weeks, 6 months and 1 year). The SF-36 quality of life questionnaire will be filled upon admission and after 3 months of follow-up in both groups. The primary and secondary endpoints will be assessed with 1 year of follow-up.

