#### Secondary objective

The secondary objective is to assess whether HBOT, along with the standard treatment of chronic diabetic foot ulcers, reduces the number of major (transtibial and transfemoral) and minor amputations (toes and forefoot) and improves the quality of life of these patients, as compared to the standard treatment alone.

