### Interventions

The patients of the HBOT group will be evaluated upon admission, after 10, 20, 30 and 35 HBOT sessions and after 6 months and 1 year, and the control group will also be assessed at equivalent periods (upon admission, after 2, 4, 6 and 7 weeks, 6 months and 1 year) to clinically evaluate the ulcers and perform specific measures using the software ImageJ, developed at the National Institutes of Health (NIH, Bethesda, Maryland). HBOT sessions will be held 1 week after randomization. The sessions will be supervised by doctors trained in hyperbaric medicine by the Brazilian Society of Hyperbaric Medicine (SBMH). The HBOT sessions will be conducted 5 days a week, being carried out with patients in a multiplace chamber at 2.5 atm absolute (ATA) and 100% O_2_, with 10 min for compression and decompression, effective sessions of 90 min, with intervals of 5 min for each 30 min of treatment. The dressings will be done in both groups with Exufiber foam Ag® (*Molnlycke*, Gotemburgo, Suécia) or Mepilex® (*Molnlycke*, Gotemburgo, Suécia), which will be chosen according to the characteristics of wounds, with silver dressings for the infected injuries and a foam with polyurethane protective layer for wounds in which granulation tissue has formed. Secondary dressings will be changed daily and the primary dressings (coverings—Exufiber foam Ag or Mepilex) will be changed every 3–5 days, as needed and in both groups. The progression of the wounds and specific treatment, such as appropriate bandage, antibiotic therapy or need of some surgical intervention, will be evaluated on a weekly basis. In both groups, a vascular surgeon will monitor the patients, and who will assess the need for surgical procedures (debridement and amputations), in addition to appropriate antibiotic therapy for each case. With regard to load relief, patients in both groups will wear orthopaedic Baruk shoes.

The SF-36 quality of life questionnaire will be filled upon admission and after 3 months of follow-up in both the groups. Laboratory examinations, such as a haemogram, erythrocyte sedimentation rate, levels of C-reactive protein, creatinine, fasting blood glucose and glycosylated haemoglobin will also be estimated only on admission.

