### Data analysis

The collected data will be stored in a Microsoft Excel 2016 spreadsheet format. After checking for errors and inconsistencies, descriptive summaries will be provided by treatment arm, including absolute and relative frequencies and measures of central tendency and variability. We will do regular monitoring, with active search by address and phone to avoid sample loss. We will use the intention-to-treat in the analysis. Blinding will be done for the researcher who will evaluate the final data and for the statistician.

Logistic regression models will be used to assess associations between the categorical variables. Both relative effects (odds ratios) and absolute effects (risk differences) will be presented with corresponding confidence intervals. Student’s *t* test or a similar non-parametric method will be used for the analysis of continuous variables. All examinations will be performed at 5% significance in the IBM SPSS® program, Version 24.0, 2016 (IBM, Armonk, NY, USA).

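### The SF-36 comparison is worded as admission against 3 months, although the quality-of-life objective is between arms; a baseline-adjusted between-arm analysis should be stated

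*Protocol article*

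**What the plan says.** The Secondary objective section asks whether HBOT added to standard treatment "improves the quality of life of these patients, as compared to the standard treatment alone". That is a contrast between arms.

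The Secondary outcome section treats its outcomes differently. For amputations and unhealed lesions it names a between-arm test: "Amputation rates and the reduction of lesions that do not heal will be assessed, with an evaluation of statistical significance between the groups". For SF-36 it says "The evaluation of the domains of the SF-36 quality of life questionnaire will also be done in both groups", and then "The data from this questionnaire upon admission and after 3 months of follow-up will be compared". The Interventions section gives the same two time points for both arms.

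The Data analysis section assigns logistic regression to categorical variables. For continuous variables it names Student's t test, or says that "a similar non-parametric method will be used for the analysis of continuous variables". It does not say whether the test is paired or two-sample, or whether it uses the 3-month score or the change, and it names no covariate.

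**The concern.** The SF-36 sentence names two time points and no contrast between arms, while its neighbour on amputations does name one. A team following the text literally could run a paired test in each arm and compare the two p-values. That does not estimate the effect of HBOT. Both arms receive the same dressings, weekly review, surgical follow-up and load-relief shoes, and the sample-size section allows for healing in up to 70% of controls by 1 year. Some improvement in quality of life in both arms is therefore plausible. If it occurs, significance in one arm only can arise by chance and be read as a benefit. The trial has no sham and SF-36 is self-reported, so the contrast needs to be clear.

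If a two-sample t test is intended, the comparison is valid. The question is then whether the admission score, which is collected anyway, is used efficiently.

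**Working it through.** **The plan's own figure.** The article gives 60 per arm, calculated for healing (70% against 90%, 80% power, 5% significance). With unpooled variance, n = (1.960 + 0.842)² × (0.7×0.3 + 0.9×0.1) / 0.2² = 58.9; with pooled variance, n = 62. The stated 60 is reproduced to within 2 patients, and power at 60 per arm is 78.9%. There is no corresponding figure for SF-36, so only n = 60 per arm carries over.

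**Assumptions.** The article gives no SF-36 standard deviation, effect size or correlation r between admission and 3 months. Tests are taken as two-sided at 5%, with no dropout.

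**Reading A: a before-after test in each arm.** Let both arms improve equally by δ SD of change, so there is no treatment effect. The chance p that one arm shows a significant improvement is the upper tail of a noncentral t with 59 df and noncentrality δ√60. The arms are independent, so P(HBOT only) = p(1−p) and P(exactly one arm) = 2p(1−p).

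| δ (SD of change) | p per arm | HBOT only | exactly one arm |
|---|---|---|---|
| 0.1 | 0.115 | 0.102 | 0.204 |
| 0.2 | 0.331 | 0.222 | 0.443 |
| 0.25 | 0.478 | 0.250 | 0.499 |
| 0.3 | 0.628 | 0.234 | 0.467 |
| 0.4 | 0.862 | 0.119 | 0.238 |
| 0.5 | 0.968 | 0.031 | 0.062 |

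The maximum of p(1−p) is 0.25, reached when p is one half. A valid two-sided between-arm test at 5% would wrongly favour HBOT 2.5% of the time. All figures are per domain.

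**Reading B: a two-sample t test.** Relative to the variance of the raw score, the residual variance v is:
- 3-month score: 1
- change score: 2(1−r)
- ANCOVA on the admission score: 1−r²

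ANCOVA against the change score is (1−r²)/[2(1−r)] = (1+r)/2, which is 0.75 at r = 0.5 and 0.85 at r = 0.7. ANCOVA against the 3-month score is 0.75 and 0.51.

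Power for an assumed 0.4 SD difference is Φ(0.4/√(2v/60) − 1.96):

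| r | 3-month score | change score | ANCOVA |
|---|---|---|---|
| 0.3 | 0.591 | 0.457 | 0.632 |
| 0.5 | 0.591 | 0.591 | 0.716 |
| 0.7 | 0.591 | 0.807 | 0.866 |
| 0.8 | 0.591 | 0.934 | 0.955 |

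For example, ANCOVA at r = 0.5 gives 0.4/√(1.5/60) = 2.530; 2.530 − 1.960 = 0.570; Φ(0.570) = 0.716. ANCOVA has the highest power in every row. Which of the two t tests comes closer to it depends on r.

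**The case against.** The strongest reply is that the article never says the comparison is made within each arm. The SF-36 sentences directly follow one on significance between the groups, the objective is explicitly comparative, and the named test is Student's t test without the word paired. A two-sample t test of change from admission to 3 months fits all of this, answers the objective and uses the admission score. Baseline adjustment of a secondary outcome could also sit in an analysis plan that is not shown. This much stands: the before-after reading is the literal one but not the only one, and the missing covariate alone would not be a defect.

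A reader might go further in three ways, none of which the article supports.
- That the baseline score is wasted. This would hold only for a t test on 3-month scores alone, which the article never names; the SF-36 sentence uses both time points.
- That adjustment lifts power from 59% to 87%. That is the gain at r = 0.7 over the same unnamed test. Over a change-score t test the gain at r = 0.7 is from 81% to 87%.
- That the SF-36 timing contradicts the abstract, where "The primary and secondary endpoints will be assessed with 1 year of follow-up", so that a 1-year questionnaire is required. The abstract, the Interventions section and the Secondary outcome section all give admission and 3 months for SF-36. The 1-year sentence is general abstract wording, and a further questionnaire would be a design request, not a correction.

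The reply does not remove the mismatch itself. The article states a comparison and a class of test, and neither tells the analyst to compare the arms on SF-36.

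**Conclusion.** The point holds in a limited form. As worded, the article does not state a between-arm SF-36 test to match its between-arm objective, and it provides only an unadjusted method for continuous data.

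On the literal before-after reading, the chance per domain of significance in the HBOT arm only, with no treatment effect, runs from about 3% to a peak of 25% over common improvements of 0.1 to 0.5 SD of change. The 25% should not be quoted without that range.

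On the two-sample reading the analysis is valid and the loss is precision. At r = 0.5 to 0.7, ANCOVA variance is 0.75 to 0.85 of that of a change-score t test, or 0.75 to 0.51 of that of a 3-month-score t test. All these figures rest on assumed improvements, effects and correlations, 60 per arm and no dropout.

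A baseline-adjusted between-arm analysis is better under either reading and costs nothing, so this is a free improvement to a secondary outcome. It does not threaten the primary analysis.

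**What to change.** In the Secondary outcome section, state that each SF-36 domain score at 3 months is compared between the HBOT and control arms. In the Data analysis section, state that this is done by ANCOVA with treatment arm and the admission score of that domain as terms, reporting the adjusted mean difference with its 95% CI. Add that within-arm changes from admission to 3 months are shown descriptively only, without being used as evidence of a treatment effect.

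The cost is a few lines of wording. Both questionnaires are already scheduled, so no data, visits or patients are added. The assessment times stay as they are.

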### Data analysis

The collected data will be stored in a Microsoft Excel 2016 spreadsheet format. After checking for errors and inconsistencies, descriptive summaries will be provided by treatment arm, including absolute and relative frequencies and measures of central tendency and variability. We will do regular monitoring, with active search by address and phone to avoid sample loss. We will use the intention-to-treat in the analysis. Blinding will be done for the researcher who will evaluate the final data and for the statistician.

Logistic regression models will be used to assess associations between the categorical variables. Both relative effects (odds ratios) and absolute effects (risk differences) will be presented with corresponding confidence intervals. Student’s *t* test or a similar non-parametric method will be used for the analysis of continuous variables. All examinations will be performed at 5% significance in the IBM SPSS® program, Version 24.0, 2016 (IBM, Armonk, NY, USA).

### Ethical aspects

This study will be based on the principles of Resolution 466/12 of the National Health Council that regulates the research involving human subjects. The patients involved shall be duly informed and clarified about the importance and purpose of the study; if patients accept to participate, they will sign an informed consent form (see supporting information). The non-participation in the study or waiver, privacy, reliability and anonymity of the participants will be guaranteed.

The study was initiated after approval by the Research Ethics Committee of the ABC University. It is registered with the Brazilian Registry of Clinical Trials (ReBEC) under the number RBR-7bd3xy.

### Adverse events

This study is being conducted in accordance with the guidelines of the Brazilian Society of Hyperbaric Medicine (SBMH) and Undersea & Hyperbaric Medical Society (UHMS), and if adverse events occur (such as dizziness, seizure,7 pneumothorax, pneumomediastinum, nauseas, middle ear barotrauma, seizure, ear pain, confinement anxiety, hypoglycemic event and shortness of breath), these will be conducted according to these guidelines, as well as be documented and published later.

## Discussion

The current study has been designed to compare the existing standard treatment for chronic foot ulcers of diabetic patients, i.e. dressings, debridement, antibiotics, load relief and their combination with HBOT. Since we do not believe in comparing the two groups with pseudotherapy, it will not be performed on any patient as described by O’Reill et al. and Londahl et al. [7, 25]. Subpressurising or pressurinsing as a placebo would alter the normal physiology of patients’ blood gases, which does not occur in standard treatment. Therefore, we believe in the power of evidence that can be provided with this proposed study model.

## Data Availability

Data and materials will be available as soon as they are collected. The datasets used and/or analysed during the current study available from the corresponding author on reasonable request. The results of the study will be published in a scientific journal, as well as via Plataforma Brasil and ReBEC.

## Abbreviations

HBOT: Hyperbaric oxygen therapy
OR: Odds ratio
SUS: Unified Health System
